## Abstract

**Background:**

Osteoarthritis (OA) is a major degenerative disease that affects the elderly. The global prevalence of OA is increasing annually. However, current treatments are unable to halt the progress of OA. At present, pharmacological treatments such as non-steroidal anti-inflammatory drugs (NSAIDs) and cyclooxygenase-2 (COX-2) inhibitors control the pain; however, there may be side effects to these medications. We hypothesized that Cortex Eucommiae (CE; *Eucommia ulmoides* Oliver) extract, which is used as a dietary supplement, may slow down or prevent OA.

**Methods:**

This is a protocol for a 12-week, multicenter, randomized, double-blind, placebo-controlled, parallel-group study to evaluate the efficacy and safety of CE extract in subjects with mild OA. One-hundred subjects with mild OA will be recruited and randomly divided in a 1:1 ratio into 2 groups. One group will receive CE extract for 12 weeks and the other group will receive placebo for 12 weeks. Outcomes will be evaluated by using the visual analog scale (VAS), Korean-Western Ontario and McMaster Universities index (K-WOMAC), Korean-Short Form health survey-36 score (KSF-36), and laboratory test results.

**Discussion:**

This clinical trial is expected to provide evidence of the efficacy and safety of CE extract as a treatment for mild OA.

**Trial registration:**

Clinical Trials.gov NCT03744611, registered on November 12, 2018, at https://clinicaltrials.gov/ct2/show/NCT03744611

## Introduction

1

Osteoarthritis (OA) is one of the major degenerative diseases that affect the elderly and is characterized by damage to the joints of the body. In OA, the joint cartilage becomes thinner and damaged, which inhibits free movement and causes pain.^[1]^ The global prevalence of OA is increasing annually as a result of the increasing age of the population. Among the elderly, approximately 9.6% of men and 18.0% of women have symptoms of OA.^[2]^ However, the progression of OA cannot be halted with the current treatments. At present, pharmacological treatments, such as non-steroidal anti-inflammatory drugs (NSAIDs) and cyclooxygenase-2 (COX-2) inhibitors, are used to control the pain associated with OA.^[3]^ However, the use of these medications carries a risk of adverse effects.^[4,5]^

*Eucommia ulmoides* Oliver has been used as a traditional herbal medicine in Asia for the treatment of various diseases.^[6]^ The efficacy and safety of *E ulmoides* against various diseases have been reported previously.^[7–11]^ Traditionally, it has been used as a pain remedy in China, and the bark of *E ulmoides* has been used as a treatment for arthritis.^[6,12]^ Recently, the effects and mechanisms of Cortex Eucommiae (CE; *E ulmoides*) extract on OA were studied in vitro, and these studies showed that CE extract inhibited inflammatory mediators.^[13,14]^ In vivo studies have identified the collagen synthesis-promoting and cartilage-protective effects of CE extract and the underlying mechanisms responsible.^[12,15]^ Thus, we will conduct a clinical trial to investigate the efficacy and safety of CE as a treatment for mild OA.

## Methods and analysis

2

### Study design

2.1

This is a 12-week, multicenter, randomized, double-blind, placebo-controlled, parallel-group study. In total, 100 participants will be recruited at Kyung Hee University Korean Medicine Hospital at Gangdong, Kyung Hee University Korean Medicine Hospital, and Dongguk University Bundang Oriental Hospital in Korea. Protocol version is ver.1.4, dated September 06, 2019. Written informed consent will be obtained from each participant before the commencement of any study-related procedure. After written informed consent has been obtained, a screening test will be conducted; subjects meeting all the eligibility criteria will be randomly allocated to either the test group or the control group at a 1:1 ratio. The test group will be instructed to consume the CE extract for 12 weeks and the control group will be instructed to consume the placebo product for 12 weeks. All enrolled subjects will receive guidance on maintaining general diet and activity levels during the study. The participants will visit the hospital four times during the study. Scheduled assessments will be conducted at screening (Week –2 to 0), baseline (Week 0), and at the end of Weeks 6 and 12. The study flow chart is shown in Figure 1.

**Figure 1 F1:**
[figure not shown]
Study flowchart.

### Recruitment

2.2

Participants will be recruited via advertisement to the public. Clinical trial recruitment posters have been posted in hospitals and subways after institutional review board approval. The poster contains brief information about the trial: purpose, method, inclusion criteria, information about the test product, predictable side effects, and information about the participating hospitals and the sponsor.

### Participants

2.3

#### Inclusion criteria

2.3.1

Subjects meeting all of the following inclusion criteria may be eligible for enrollment in the study:

Male or female subjects between 40 and 75 years of age, inclusiveSubjects with a visual analog scale (VAS) score of more than 30 mmSubjects with Kellgren and Lawrence grade I or II determined by X-raySubjects who agree to participate in the clinical trial voluntarily and sign the informed consent form (ICF)

#### Exclusion criteria

2.3.2

Subjects who meet any of the following exclusion criteria will be excluded from participation in the study.

Subjects with joint space of less than 2 mm determined by X-raySubjects with Kellgren and Lawrence grade III or higher, with osteophytes, irregularly-shaped auricular surfaces, or subchondral bone cysts visible by X-raySubjects diagnosed with inflammatory arthritis (rheumatoid arthritis, fibromyalgia, systemic lupus erythematosus, septic arthritis, gout), or articulation fracture and an abnormal erythrocyte sedimentation rate (ESR) and C-reactive protein (CRP) levelSubjects diagnosed with cardiovascular diseases, immune diseases, infectious diseases, and tumorsSubjects with gastrointestinal diseasesSubjects with uncontrolled hypertension (blood pressure ≥160/100 mmHg)Subjects with uncontrolled diabetes mellitus (fasting glucose level ≥180 mg/dL)Subjects with abnormal AST or ALT levels (three times higher than the upper limit of normal)Subjects with abnormal creatinine levels (2 times higher than the upper limit of normal)Subjects who are pregnant or breastfeeding, or who plan to be pregnant within the next 3 monthsSubjects using OA treatment drugs or dietary supplements in the 2 weeks prior to screeningSubjects receiving OA treatment therapy in the 2 weeks before screeningSubjects with psychiatric disorders (schizophrenia or depressive disorder) or who show signs of drug abuseSubjects who have participated in another clinical trial in the 3 months prior to screeningSubjects with a history of hypersensitivity to the investigational productSubjects judged as having trial participation-related difficulties by the investigator

#### Handling of withdrawal and dropout

2.3.3

According to the Declaration of Helsinki, participants may withdraw from the study at any time without providing a reason. Participants may be withdrawn from the study to ensure their safety by the investigator. Investigators may withdraw a participant from the study for any of the following reasons:

A significant protocol violationOccurrence of a serious adverse event (SAE) or adverse event (AE)Subject's refusal to participate in the studySubject withdraws consentLoss to follow-upSubject is unable to consume the test or placebo productReceipt of any medicine or treatments that could interfere with study participationWithdrawal from the study for safety reasons as determined by the investigatorPregnancy

### Randomization and blinding

2.4

The randomization sequence will be generated by Jaseng Spine and Joint Research Institute of Jaseng Medical Foundation, and Microsoft Excel 2010 (Microsoft Inc., USA) will be used to create a blocked randomization list. Randomization codes will be provided in envelopes and kept at each center; randomization will be performed at each center. Eligible participants will be randomly assigned to either the test group or the placebo group in a 1:1 ratio. This study design is double-blind; therefore, both the investigators and the subjects will be blinded during the study. To maintain the blinding, the appearance of the test and placebo product will be identical. The study blind will be broken in situations such as SAEs.

### Intervention

2.5

One-hundred subjects with mild OA will be recruited and randomly divided into 2 groups; and each subject will receive CE capsules or placebo capsules as dictated by the randomization sequence. Participants will be instructed to consume 1 g/day of *E ulmoides* Oliver extract (2 capsules/day) or placebo (2 capsules/day), by taking 1 capsule in the morning and 1 capsule at night, for 12 weeks. The test and placebo capsules have been manufactured by Nutribiotech Co., Ltd. (Icheon-si, Gyeonggi-do, Korea), a GMP-certified manufacturing facility. The 550 mg test capsule is composed of *E ulmoides* Oliver extract 500 mg, crystalline cellulose 41.75 mg, silica 2.75 mg, and magnesium stearate 5.50 mg. The 550 mg placebo capsule is composed of lactose powder 438.24 mg, caramel color 27.50 mg, purified water 43.59 mg, ethanol 4.40 mg, crystalline cellulose 28.02 mg, silica 2.75 mg, and magnesium stearate 5.50 mg.

### Concomitant drugs and therapies

2.6

The following drugs, foods, and therapies will be restricted during the intervention period.

OA medication (eg, Joins tab., etanercept, celecoxib, and hyaluronic acid)Aspirin and anti-inflammatory analgesic drugs, corticosteroids, anti-rheumatic drugsPenicillamine, diacerein, and pyrazinobutazoneCyclophosphamideKorean traditional medicinal herbs used to treat OA (eg, Clematidis Radix and Trichosanthis Radix)Dietary supplements for joint health (eg, glucosamine, *Perna canaliculus* oil complex, rosehip powder, and *Perilla frutescens*)OA therapies (physical therapy, Korean traditional medical treatments such as acupuncture, cupping therapy, and moxibustion)

Information about concomitant drugs and therapies will be recorded in the case report form (CRF).

### Outcomes

2.7

#### Primary outcomes

2.7.1

The primary outcomes will be the VAS score, the Korean-Western Ontario and McMaster Universities (K-WOMAC) index, and the Korean-Short Form Health Survey 36 (KSF-36) score.

VAS will be used to measure changes in joint pain at 6 and 12 weeks after treatment administration and compare it with the baseline score.The K-WOMAC index will be used to measure changes in joint pain and function at 6 and 12 weeks after treatment administration and compare it with the baseline index.The KSF-36 score will be used to measure changes in physical and mental functions at 6 and 12 weeks after treatment administration and compare it with the baseline score.

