### Sample size

2.9

The sample size was calculated in accordance with the method described by Giordano et al.^[16]^ In their study, the VAS scores for resting pain in the treatment group were significantly decreased from 42.0 ± 24.2 mm to 25.4 ± 19.9 mm (mean ± standard deviation) over 12 weeks. Conversely, the VAS scores for resting pain in the placebo group were increased from 40.9 ± 23.6 mm to 41.0 ± 20.5 mm during the same period. On the basis of these results, we suppose that the change in the treatment group will be –16.6 mm and that in the placebo group will be 0.1 mm. The sample size for this study has been determined using the following parameters:

Superiority testLevel of significance, α = 0.05Two-sided testβ = 0.2, power of test = 80%Ratio of the number of subjects in the test and placebo groups, λ = 1, n_t_ (subject number of the test group) = λn_c_ (subject number of the placebo group)Difference between the groups, Δ = 16.7Standard deviation, *σ* = 27.04 (in both groups)

A sample size of 42 subjects per group was calculated, and on the assumption of a dropout rate of 15%, 50 participants will be recruited into each group.

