### Statistical analysis

2.10

Statistical analyses will be computed by using SPSS version 24.0 (SPSS Inc., Chicago, IL). The collected data will be analyzed by using full analysis set analysis, per protocol set analysis, and safety set analysis methods. Missing data will be analyzed by the last observation carried forward method. Baseline characteristics between the test and placebo groups will be evaluated by using the 2-sample *t* test for continuous variables. Categorical variables will be evaluated by using the Chi-square test, Fisher exact test, or McNemar test, and expressed as frequencies and percentages. A paired *t* test will be used to compare the effect within each group both before and after the intervention. ANCOVA and 2 sample *t* tests will be used to compare the net changes between the 2 groups. Skewed variables will be analyzed by using a logarithmic transformation or Wilcoxon rank sum test. Treatment-emergent adverse events (TEAEs) will be coded using the Medical Dictionary for Regulatory Activities (MedDRA) and the percentage of subjects with AEs will be determined and evaluated by using Chi-square test or Fisher exact test. The results will be expressed as the mean ± standard deviation (SD) values and a *P* value of <.05 will be considered to indicate a statistically significant difference.

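### Three unranked primary outcomes at two time points share a flat P<.05 with no success rule, while the sample size covers only the 12-week change in VAS resting pain, so neither a 5% error rate nor 80% power is secured for the primary set as a whole

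*Protocol article*

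**What the plan says.** Section 2.7.1 (Primary outcomes) of the protocol article states: "The primary outcomes will be the VAS score, the Korean-Western Ontario and McMaster Universities (K-WOMAC) index", and the same sentence adds the KSF-36 score as the third. No outcome is put ahead of another. Each is then given the same two time points. For pain, "VAS will be used to measure changes in joint pain at 6 and 12 weeks after treatment administration"; for quality of life, "The KSF-36 score will be used to measure changes in physical and mental functions at 6 and 12 weeks after treatment administration"; K-WOMAC is worded in the same way. That makes 3 outcomes × 2 times = 6 primary comparisons.

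Section 2.10 (Statistical analysis) says of the between-group tests: "ANCOVA and 2 sample *t* tests will be used to compare the net changes between the 2 groups". The only decision threshold is a P "value of <.05 will be considered to indicate a statistically significant difference". There is no testing order or division of alpha, and nothing says whether one primary outcome or all of them must succeed.

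Section 2.9 (Sample size) rests on a cited study in which "the VAS scores for resting pain in the treatment group were significantly decreased" over 12 weeks. From it the section takes a difference of 16.7 mm, an SD of 27.04 mm, two-sided α of 0.05 and 80% power, giving 42 per group, or 50 per group with 15% dropout. It gives no effect size or power for K-WOMAC, KSF-36 or Week 6.

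**The concern.** The article fixes a primary set of six comparisons but sizes the trial on one of them, and it leaves open what result would count as a positive trial. The two natural success rules fail in different ways. If any one primary result below .05 is enough, an ineffective product has a clearly greater than 5% chance of being declared different from placebo. If all three outcomes must succeed, the false-positive risk is controlled, but the 80% power in section 2.9 does not describe the chance of success. With no rule stated, the choice could be made after the results are known.

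There is also a mismatch within the VAS outcome. Section 2.7.1 refers to joint pain, while the planning values in section 2.9 are for resting pain. The one outcome that was sized is therefore not clearly the one that will be measured.

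**Working it through.** **Inputs from the article.** Difference Δ = 16.7 mm, SD σ = 27.04 mm, two-sided α = 0.05, power 80%, 1:1 allocation, dropout 15% (section 2.9). Three outcomes at two times (section 2.7.1). Threshold P<.05 (section 2.10).

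**Inputs assumed.** The correlation between test statistics, taken as equal for every pair, and the power for K-WOMAC and KSF-36. The article gives neither, so ranges are shown.

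**1. The plan's own figure.**
- n per group = 2σ²(1.960 + 0.842)²/Δ² = 41.15, rounded up to 42.
- Dropout: 42/(1 − 0.15) = 49.4, rounded up to 50.
- Power at 42 per group: standard error = 27.04 × √(2/42) = 5.90; 16.7/5.90 = 2.83; Φ(2.83 − 1.96) = 80.8%. The t-based value is 79.9%.

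The stated 42 and 50 are reproduced. They are right for one comparison at unadjusted 0.05.

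**2. Success if any one primary result is significant.** With k independent tests and no true effect, the familywise error is 1 − 0.95^k.
- k = 3 (three outcomes, one time point): 1 − 0.95³ = 14.3%.
- k = 6 (three outcomes, two times): 1 − 0.95⁶ = 26.5%.

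With equally correlated normal test statistics, each tested two-sided at 0.05:

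| Correlation | 3 tests | 6 tests |
|---|---|---|
| 0 | 14.3% | 26.5% |
| 0.5 | 12.5% | 20.7% |
| 0.8 | 9.8% | 13.9% |

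The error is therefore about two to three times nominal for three tests and about three to five times for six. Under this rule the power for VAS at Week 12 is unchanged.

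**3. Success only if all three outcomes are significant at Week 12.** A false claim then requires every test to reject, so the error rate stays at or below 5%. If each outcome has 80% power, the joint power is:
- correlation 0: 0.8³ = 51%
- correlation 0.5: 61%
- correlation 0.7: 66%
- correlation 0.9: 72%

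Using 80.8% for each outcome, the normal-approximation power at 42 per group, moves the range only to 53% to 73%.

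**4. VAS at Week 12 as the sole primary comparison.** Step 1 applies unchanged: error 5%, power about 80%, 42/50 per group.

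**The case against.** The best defence is that this is a condensed article. An analysis plan may exist, and testing order and alpha allocation are often left to it. The P<.05 sentence also reads as a general reporting convention, not as a statement that each primary result is confirmatory by itself. This has force: the absence of a multiplicity rule is not an error in its own right. It does not dispose of the point. The article itself declares three primary outcomes at two times and sizes the trial on one of them. Of the usual rules an unseen plan might add, dividing alpha or requiring all three would leave the primary set with less than the stated power. A hierarchy headed by VAS at Week 12 would fit the calculation, but section 2.7.1 gives no ranking.

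Three stronger readings are tempting and are not supported.
- A reader might infer that the 5% error rate and the 80% power both fail together. They fail under different rules: any-win inflates error without lowering VAS power, and all-win lowers power without inflating error. For VAS at Week 12 alone, both figures hold.
- A reader might count ten tests by splitting K-WOMAC into pain and function and KSF-36 into physical and mental. The article names one index and one score; those words describe what the instruments measure, and no subscale is declared primary.
- A reader might cite the power lost under a Bonferroni correction as a failure of the plan. The plan does not propose that correction.

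It is also fair to say that the correlations are unknown and that pain, function and quality of life are likely to be correlated. That reduces the inflation, but even at 0.8 the any-win error is about 10% for three tests and 14% for six.

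**Conclusion.** The point stands as a gap between the declared primary set and the calculation behind it. The sample size is arithmetically correct for one comparison, the 12-week change in VAS resting pain. For the set as a whole, nothing in the article secures either operating characteristic.

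- Any-win rule: familywise error about 10% to 14% for three outcomes at one time point and 14% to 26% for six comparisons, with assumed pairwise correlation from 0.8 down to 0.
- All-three rule at Week 12: error at or below 5%, power about 51% to 72%, assuming 80% power for each outcome and correlation from 0 to 0.9.

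The exact figures depend on those assumptions; the direction holds throughout the ranges. It should not be inferred that this trial measures resting pain. That term appears only in the account of the cited study in section 2.9, and the two sections need reconciling.

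**What to change.** Before unblinding:
1. Name change from baseline in joint-pain VAS at Week 12 as the single primary comparison. This fits the existing 42 evaluable and 50 recruited per group.
2. Reconcile joint pain in section 2.7.1 with resting pain in section 2.9. If the VAS in this trial is not resting pain, say why the planning values still apply.
3. Make K-WOMAC and KSF-36 at Week 12 key secondary outcomes, tested in a pre-stated fixed order at two-sided 0.05, each only if the one before succeeds.
4. Treat Week 6 results as supportive.

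If the sponsor prefers to keep all three as primary, that is legitimate, but the protocol must then state the success rule and restate the power it gives.

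The recommended route needs no extra participants or visits. Its price is that a lone K-WOMAC or KSF-36 result could no longer be claimed as primary success. It is also more than a wording change: the protocol is already at version 1.4 and recruitment posters are up, so demoting two primary outcomes must be a dated, justified endpoint amendment made without knowledge of results by group.

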#### Secondary outcomes

2.7.2

Subject's Global Impression of Change scale score: The change in activity limitations, symptoms, emotions, and overall quality of life, as related to painful conditions, which will be assessed by the subjectInvestigator's Global Impression of Change scale score: The change in activity limitations, symptoms, emotions and overall quality of life, as related to painful conditions, which will be assessed by the investigatorESR, to measure changes in blood inflammatory markers at 12 weeks after treatment administration and compare it with baseline ESRCRP level, to measure changes in blood inflammatory markers at 12 weeks after treatment administration and compare it with the baseline level

#### Safety outcomes

2.7.3

The safety outcomes will be AEs, laboratory test results, vital signs (blood pressure and heart rate), weight, and electrocardiography results. An AE is defined as any unexpected occurrence that is not necessarily related to any procedure during the study. The investigator has the responsibility to report all AEs and follow up the AEs until resolved. The relationship between the AEs and the investigational product will be evaluated by the investigator. AE report forms will be completed for all the AEs. The signs and symptoms of the AEs will be described in detail, including the date of onset, duration, severity, action taken, relationship to the investigational product, specific therapy, and outcome. If SAEs occur during the study, the investigator will immediately report the SAEs to the sponsor and the IRB. The following laboratory tests will performed by the clinical laboratory at each center: complete blood count (hemoglobin, hematocrit, and white blood cells [WBC], red blood cells [RBC], platelets, neutrophils, lymphocytes, monocytes, eosinophils, and basophils), blood chemistry tests (blood urea nitrogen [BUN] and levels of aspartate aminotransferase [AST], alanine aminotransferase [ALT], total cholesterol, low-density lipoprotein [LDL]-cholesterol, high-density lipoprotein [HDL]-cholesterol, triglyceride, glucose, total protein, creatinine, uric acid, Na, K, Cl, and Ca), urine tests (specific gravity [SG], pH, and levels of glucose, ketone, bilirubin, urobilinogen, erythrocytes, leukocytes, protein, and nitrite).

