
This trial has some limitations. First, the subjects may be exclusively Korean. Therefore, the data from this clinical trial cannot be applied to other ethnic groups. Second, owing to the small sample size, the results of this study cannot be generalized. However, few clinical trials have been conducted on the effects of CE on OA. Therefore, despite these limitations, this trial is expected to demonstrate the efficacy and safety of CE for the treatment of patients with mild OA. Furthermore, the results of the study will serve as a foundation for the development of CE as a dietary supplement.

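### The adverse event definition makes unexpectedness a condition, so read literally it leaves foreseeable side effects out of the adverse event count

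*Protocol article*

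**What the plan says.** Protocol article, section 2.7.3 (Safety outcomes), defines the term once: "An AE is defined as any unexpected occurrence that is not necessarily related to any procedure during the study". No other section gives a different or broader definition.

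The same section sets the collection duty: "The investigator has the responsibility to report all AEs and follow up the AEs until resolved". It also requires an AE form for each AE and an investigator's assessment of its relationship to the investigational product. AEs are one of several safety outcomes: "The safety outcomes will be AEs, laboratory test results, vital signs (blood pressure and heart rate), weight, and electrocardiography results".

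Section 2.2 (Recruitment) says that the poster carries "information about the test product, predictable side effects, and information about the participating hospitals and the sponsor".

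Section 2.10 (Statistical analysis) states how AEs are compared: "the percentage of subjects with AEs will be determined and evaluated by using Chi-square test or Fisher exact test".

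The Discussion sets the ambition: "this trial is expected to demonstrate the efficacy and safety of CE for the treatment of patients with mild OA".

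**The concern.** A definition of an AE normally turns on whether the occurrence is unfavourable. Whether it was foreseen is a separate attribute, judged after the event has been recorded. Here being unexpected is the condition for being an AE at all, and nothing requires the occurrence to be untoward. The sentence is therefore too narrow in one respect (foreseeable harms are out) and too wide in another (a harmless surprise is in).

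The definition fixes the numerator of the AE comparison. Events that were never recorded cannot be recovered at analysis. With three centres, one may apply the wording strictly and another may record everything, so that ascertainment differs by centre. This is a matter of what the article states, not of detail that a condensed article leaves out.

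**Working it through.** **Step 1. What the definition admits.** It has two parts: the occurrence is unexpected, and it need not be related to a study procedure. The second part removes a causality requirement. It does not remove the first part, so unexpectedness remains necessary.

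**Step 2. Whether other text widens it.** The duties to report, follow up and complete a form for all AEs operate on events that are already classed as AEs. They cannot bring in an event that the definition leaves out.

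**Step 3. Whether the excluded class exists.** Section 2.2 refers to "information about the test product, predictable side effects" as poster content. The article thus accepts that some side effects are foreseeable, but it does not name them. Under Step 1 they are not AEs.

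**Step 4. Where the count is used.** Section 2.10 compares the percentage of subjects with AEs by Chi-square or Fisher exact test. A subject drops out of that percentage only if every event that subject had goes unrecorded.

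**Step 5. Whether the effect can be sized.** The plan has no AE figure to reproduce. The one relevant number is the group size in section 2.9. That calculation reproduces: 2 × (1.960 + 0.842)² × 27.04² / 16.7² = 41.2, rounded up to 42, and 42 / 0.85 = 49.4, rounded up to 50 per group. It has no bearing on the definition. The AE rate in each group and the share of expected events are not given.

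The following figures are illustrations under assumptions only. Suppose the true counts of subjects with an AE were 10 of 50 on extract and 4 of 50 on placebo.

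| Assumed loss from the definition | Extract | Placebo | Difference | Uncorrected Chi-square p |
|---|---|---|---|---|
| None | 10/50 = 20% | 4/50 = 8% | 12 points | 0.08 |
| Half in each group | 5/50 = 10% | 2/50 = 4% | 6 points | 0.24 |
| 6 on extract, none on placebo | 4/50 = 8% | 4/50 = 8% | 0 points | 1.00 |
| None on extract, half on placebo | 10/50 = 20% | 2/50 = 4% | 16 points | 0.01 |

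The difference can shrink, vanish or widen, depending on where the unrecorded events fall. In the second row the ratio of the two percentages stays at 2.5.

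**Step 6. Equal proportional loss over a range of rates.** With 50 per group and two-sided α = 0.05, power = Φ[(d − 1.96 × se₀) / se₁]. Here d is the difference in rates, se₀ is the standard error at the pooled rate and se₁ is the unpooled standard error. For 10% v 20%: d = 0.10, se₀ = √(0.15 × 0.85 × 2/50) = 0.0714, se₁ = √(0.10 × 0.90/50 + 0.20 × 0.80/50) = 0.0707, which gives Φ(−0.565) = 0.286.

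| Assumed true rates | No loss | 25% lost | 50% lost |
|---|---|---|---|
| 5% v 15% | 0.383 | 0.294 | 0.207 |
| 10% v 20% | 0.286 | 0.218 | 0.155 |
| 20% v 30% | 0.209 | 0.158 | 0.114 |

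Power for a ten-point difference is low to begin with and falls further when events are lost equally in both groups.

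**The case against.** The strongest reply is that this is a condensed article. It cites a protocol at version 1.4, and centres work from that document and its case report form, neither of which is shown. *Unexpected* may be a loose rendering of *untoward* or *unintended*. The context lends this some support: the sentence drops causality in the manner of a broad definition, relationship to the product is assessed for AEs, and nothing lists expected reactions or tells anyone to screen for them. The poster in section 2.2 is not linked to AE recording. This reply stands as a limit. It shows that the undercount depends on literal application, but it does not make the printed definition right.

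Four stronger readings are tempting, and the documents do not support them.

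- *The centres will fail to record expected reactions.* This cannot be known from the article.
- *The comparison is biased towards no difference.* Blinded investigators would apply the same filter in both groups, and foreseeable events can also occur on placebo. The 8% v 8% row above arises only if every lost event is on extract, and even the full 10/50 v 4/50 contrast is not significant at 0.05.
- *The reference to a study procedure contradicts the later assessment against the investigational product.* The two are compatible: one says that relatedness to a procedure is not required, the other asks for a causality judgement on each AE.
- *Treatment-emergent is left undefined.* That definition can properly sit in the full protocol or the SAP.

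A delayed safety signal is also not established. Serious events go immediately to the sponsor and the review board, and the laboratory, vital-sign, weight and electrocardiography data are collected whatever the AE definition says.

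**Conclusion.** The point holds as a defect of definition. As printed, section 2.7.3 makes unexpectedness necessary for an AE, leaves out a class of event that section 2.2 recognises, and passes the resulting count to the between-group test in section 2.10. If the wording is applied literally, AEs could be undercounted and recording could differ between centres.

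The effect on the comparison cannot be determined in size or direction, and the illustrations rest wholly on assumed rates. The loss is confined to the AE outcome. No stated figure, efficacy outcome or sample size changes. The conclusion assumes that the full protocol does not already carry a broader definition, which should be checked first.

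**What to change.** In section 2.7.3, replace the definition with: any untoward medical occurrence in a participant, whether or not expected and whether or not considered related to the investigational product or a study procedure. If expectedness is needed for reporting, record it as a separate attribute of each AE.

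Check that protocol version 1.4 and the guidance for the case report form carry the same wording, so that the three centres record events by one rule. If sites have already recorded events under the narrower wording, state in the report from which date the new definition applied.

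The cost is one sentence and a slightly higher recorded AE count. If *untoward* was meant all along, the change alters nothing in practice.
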